# Effects of cyclosporine A pretreatment of deceased organ donors on kidney graft function (Cis-A-rein): study protocol for a randomized controlled trial

**DOI:** 10.1186/s13063-018-2597-4

**Published:** 2018-04-17

**Keywords:** Cyclosporine A, Preconditioning, Transplantation, Kidney, Delayed graft function

## Abstract

**Background:**

Renal transplantation represents the treatment of choice of end-stage kidney disease. Delayed graft function (DGF) remains the most frequent complication after this procedure, reaching more than 30%. Its prevention is essential as it impedes early- and long-term prognosis of transplantation. Numerous pharmacological interventions aiming to prevent ischemia-reperfusion injuries failed to reduce the rate of DGF. We hypothesize that cyclosporine as an early preconditioning procedure in donors would be associated with decreased DGF.

**Methods:**

The Cis-A-rein study is an investigator-initiated, prospective, multicenter, double-blind, randomized, controlled study performed to assess the effects of a donor preconditioning with cyclosporine A on kidney grafts function in transplanted patients. After randomization, a brain dead donor will receive 2.5 mg kg^−1^ of cyclosporine A or the same volume of 5% glucose solution. The primary objective is to compare the rate of DGF, defined as the need for at least one dialysis session within the 7 days following transplantation, between both groups. The secondary objectives include rate of slow graft function, mild and severe DGF, urine output and serum creatinine during the first week after transplantation, rate of primary graft dysfunction, renal function and mortality at 1 year. The sample size (*n* = 648) was determined to obtain 80% power to detect a 10% difference for rate of DGF at day 7 between the two groups (30% of the patients in the placebo group and 20% of the patients in the intervention group).

**Discussion:**

Delayed graft function is a major issue after renal transplantation, impeding long-term prognosis. Cyclosporine A pretreatment in deceased donors could improve the outcome of patients after renal transplantation.

**Trial registration:**

ClinicalTrials.gov, ID: NCT02907554 Registered on 20 September 2016.

**Electronic supplementary material:**

The online version of this article (10.1186/s13063-018-2597-4) contains supplementary material, which is available to authorized users.

## Background

Renal transplantation represents a major treatment for end-stage kidney disease patients. In France, the number of kidney transplantations increases to reach more than 3000 per year [1]. The most frequent complication of such a procedure is the delayed graft function/slow graft function (DGF/SGF). Delayed graft function is commonly defined as the need for at least one dialysis session within the first week after transplantation [2]. Delayed and slow graft functions account for 30% and 40–60% of renal transplantations, respectively, with variations depending on the presence of risk factors [2–4]. Alteration of the long-term renal function represents the main problem related to these complications [5]. The pathophysiology of DGF/SGF involves ischemia-reperfusion injuries [6]. During the transplantation procedure, the kidneys suffer from warm (harvesting and grafting before vascular anastomosis) and cold ischemia (preservation) followed by reperfusion. The mechanisms of renal damages are complex, multifactorial and interdependent leading to biochemical, structural and functional alterations. The association of hypoxic and ischemia-reperfusion injuries decreases renal blood flow, increases oxidative stress and triggers the release of pro-inflammatory mediators which activate leukocyte adhesion and immune phenomena. It seems that reperfusion induces sustained abnormalities leading to tissue damage characterized by apoptotic and necrotic cell death and finally renal dysfunction. To our knowledge, several clinical interventions aiming to decrease such damages have reported conflicting results on the incidence of DGF [7, 8].

Mitochondria play a central role in the pathophysiology of ischemia-reperfusion injuries. The homeostatic disturbances associated with this phenomenon lead to the formation of the permeability transition pore (PTP) and its subsequent opening between the internal and the external mitochondrial membranes. This has consequences for mitochondrial depolarization, energetic failure, oxidative stress and the release of proapoptotic factors. The composition of the PTP is debated and the only certainty is the presence of a regulatory protein, cyclophillin D. The inhibition of the binding of this protein to the PTP prevents the opening of this channel, and potentially the deleterious biochemical cascade.

Cyclosporine A is largely administered for immunosuppression that is mediated by the inhibition of calcineurin. This medication served for the development of solid organ transplantation, especially kidneys. Subsequent research unveiled other properties including the inhibition of the opening of the PTP by its binding to cyclophilin D. This property was used to decrease ischemia-reperfusion injuries in different organs and experimental models [9, 10]. In a rabbit model of cardiac arrest induced by asphyxia, cyclosporine A decreased the magnitude of cardiac, liver and renal dysfunction [11]. These results were associated with a reduction in the PTP opening and a restoration of oxidative phosphorylation. Cyclosporine A also improved the organ and the mitochondrial functions as well as histological injuries in models of liver and cardiac transplantation [12]. Three studies reported conflicting results concerning the potential benefits of cyclosporine A in rat kidney transplantation models [13–15]. This discrepancy could be explained by a prolonged cold ischemia time (24 h) in the negative study [15]. Based on these data, we hypothesize that a cyclosporine A preconditioning in brain-dead donors, by inhibiting the PTP opening, will improve the outcome of patients undergoing renal transplantation. The primary objective of the study is to evaluate the effects of such a preconditioning treatment administered in organ donors with a beating heart on the rate of DGF in the recipient, defined by the need of at least one dialysis session during the first week after transplantation. The main secondary objectives are the rate of SGF during the first week, urine output and serum creatinine during the first week, the rate of primary graft dysfunction, graft function and the mortality at 1 year after transplantation.

## Methods/design

### Trial design

“Cis-A-Rein” is an investigator-initiated, prospective, multicenter, double-blind, randomized controlled versus placebo study performed to assess the effects of a donor preconditioning with cyclosporine A on kidney grafts function in transplanted patients. After randomization, cyclosporine A or a placebo will be given to brain-dead patients with a beating heart before organ harvesting. The function of the kidneys procured from these patients will be analyzed in the recipients of this graft. The study protocol was designed using the recommendations of the Consolidated Standards of Reporting Trials (CONSORT) Statement. It is described as required by the SPIRIT guidelines to ensure consistent reporting of clinical trials (Additional file 1). Figure 1 reports the overview of the enrollment, interventions and assessments of the trial.

**Fig. 1 Fig1:**
[figure not shown]
Overview of enrollment, interventions and assessments of the Cis-A-rein study. *DGF* delayed graft function, *SGF* slow graft function

### Selection of participants

➢ Donor inclusion criteria○ Brain death with a beating heart○ Age between 18 and 70 years➢ Donor exclusion criteria○ Contra-indications for organ harvesting (infections, cancer, etc.)○ Chronic kidney disease○ Refusal of organ donation by the donor (confirmed by the French National Register or reported by the next-of-kin)○ Inclusion in another protocol➢ Recipient inclusion criteria○ Age between 18 and 70 years○ Indication of kidney transplantation○ Written informed consent given➢ Recipient exclusion criteria○ Indication of double kidney transplantation○ Indication of multiorgan transplantation

### Randomization and blinding

Computer-generated randomized lists will be drawn up before the onset of the study using a permuted block design, under the responsibility of the Clinical Research Unit (Unité Aide Méthodologique à la Recherche Clinique, AP-HM, France). Randomization (1:1 allocation ratio) will be stratified by center (*n* = 16) and the number of kidneys per donor (two modalities, one or two). Randomization is centralized, web-based and accessible 24 h a day according to the allocation list. A randomization number will be allocated to each patient. The intensivist and the nurse in charge of the donor with a beating heart will be blinded regarding the allocation of treatment (preparation by an intensive care unit (ICU) nurse or a clinician not in charge of the donor). The statistician, the transplanted patients and the clinicians in charge of the transplanted patient will all be blinded concerning the treatment allocation.

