### Trial intervention

After randomization, donors with a beating heart will receive a single dose of 2.5 mg kg^−1^ of cyclosporine A (diluted to obtain a 5 mg mL^−1^ concentration corresponding to an infusion of 0.5 mL kg^−1^; Sandimmun**®**, Novartis Pharma, Rueil-Malmaison, France) or an equivalent volume of placebo (glucose 5% solution 0.5 mL kg^−1^) in the 2 h before the harvesting of kidneys in the operating theater. The management of the donors, the organs and the transplanted patients will be performed according to national guidelines [16] similarly in both groups.

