#### Data analysis

The data will be analyzed using SPSS version 17.0 software. The patients found to be eligible but not included in the study will be described and compared with the included patients. The patients who present at least one of the following conditions will be not in the final analysis: patients inappropriately included despite not providing consent and patients who remove their consent. The full analysis population (including all subjects who will be randomized and will be at least evaluated at baseline) will be used in the primary analysis, and the per-protocol population (including all subjects who will be randomized and will not have major protocol deviations) will be used in the secondary analysis to assess the robustness of the results. No interim analysis is planned. The normality of these parameters will be estimated using frequency histograms and the Shapiro test. The baseline parameters will be described for the two groups (“control” and “intervention”).

The analysis of the primary endpoint will consider the proportion of DGF for each group. These proportions will be compared using the chi^2^ test or Fisher’s exact test for categorical variables (primary analysis). Multivariate analysis (secondary analysis) using logistic regression models will be performed to determine variables potentially linked to DGF (donor’s variables: age, norepinephrine use, diabetes, high blood pressure; procurement variables: cold and warm ischemia durations; recipient’s variables: weight, dialysis duration).

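### Randomization is stratified by center and kidneys per donor, but the primary DGF test ignores both: valid on this account, slightly conservative, and cheap to improve

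*Protocol article*

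**What the plan says.** Protocol article, Randomization and blinding: "Randomization (1:1 allocation ratio) will be stratified by center (*n* = 16) and the number of kidneys per donor", the second factor having two levels. With 16 centers this makes up to 16 × 2 = 32 strata, filled by permuted blocks.

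Protocol article, Data analysis, on the primary endpoint: "The analysis of the primary endpoint will consider the proportion of DGF for each group". Then: "These proportions will be compared using the chi^2^ test or" Fisher's exact test. This is labelled the primary analysis, and no stratification factor is mentioned.

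Same section, on the only adjusted analysis: "Multivariate analysis (secondary analysis) using logistic regression models will be performed to determine variables potentially linked to DGF". The donor and procurement terms are "age, norepinephrine use, diabetes, high blood pressure; procurement variables: cold and warm ischemia durations", and the recipient terms are "variables: weight, dialysis duration". Treatment arm, center and number of kidneys are not on the list.

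Trial intervention: the donor is dosed after randomization, "in the 2 h before the harvesting of kidneys in the operating theater". The Background places warm ischemia at harvesting and grafting and cold ischemia at preservation. Both durations therefore arise after randomization and dosing.

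**The concern.** Blocking within center and number of kidneys balances the arms on those factors. If DGF rates differ between strata, that balance makes the treatment difference less variable than an unstratified test assumes. The chi-square test then uses a standard error that is slightly too large and gives up some power in a trial planned at only 80%.

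The secondary model does not visibly fill the gap. As printed, it looks for predictors of DGF and is not set up as an adjusted treatment comparison. If it were later used for that purpose, it would lack the strata and would condition on variables measured after dosing.

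The article names the test, labels it primary and lists the covariates. These are stated choices, so the point is not one left to a statistical analysis plan.

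**Working it through.** **1. The plan's own figure.** Inputs from the Sample size section: 30% against 20% DGF, two-sided alpha 0.05, 80% power. With pooled variance and no continuity correction:

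n per arm = [1.960 × √(2 × 0.25 × 0.75) + 0.842 × √(0.30 × 0.70 + 0.20 × 0.80)]² / 0.10² = 293.2, rounded up to 294.

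The total is 588, as stated, and power at 294 per arm is 80.1%. For losses, 294 × 1.1 = 323.4, rounded up to 324 per arm, or 648, as stated. The calculation is for an unstratified test, which agrees with the planned chi-square.

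**2. What ignoring center costs, by formula.** The article gives no between-center variation in DGF, so SDs of 5, 10 and 15 percentage points around the 25% average are assumed. Share of outcome variance lying between centers: x = SD² / (0.25 × 0.75). Nominal standard error of the difference: √(2 × 0.1875 / 294) = 0.0357, so the planned effect is 0.10 / 0.0357 = 2.80 standard errors. With balance inside centers the true standard error is the nominal one times r = √(1 − x). Then:

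- chi-square: type I error = 2 × [1 − Φ(1.96 / r)]; power = Φ[(2.80 − 1.96) / r]
- stratified test: power = Φ(2.80 / r − 1.96)

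| Assumed center SD | x | r | Chi-square type I error | Chi-square power | Stratified power | Gain (points) |
|---|---|---|---|---|---|---|
| 5 points | 1.3% | 0.993 | 4.8% | 80.1% | 80.5% | 0.4 |
| 10 points | 5.3% | 0.973 | 4.4% | 80.6% | 82.1% | 1.5 |
| 15 points | 12.0% | 0.938 | 3.7% | 81.5% | 84.7% | 3.3 |

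As extra effective sample size, 1/(1 − x) − 1 is 1.4%, 5.6% and 13.6%.

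**3. Simulation.** Set-up: 294 donors with two recipients each, 16 near-equal centers, arms balanced within center, no correlation between recipients of one donor, 6,000 runs per setting. Monte Carlo error is about 0.3 points for type I error and 0.5 for power. CMH is the Cochran-Mantel-Haenszel test stratified by center.

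| SD of center log-odds | 90% range of center DGF rates, placebo | Type I error, chi-square / CMH | Power, chi-square / CMH |
|---|---|---|---|
| 0 | 30% | 5.3% / 5.4% | 80.3% / 80.2% |
| 0.3 | 20% to 41% | 4.5% / 4.5% | 80.5% / 80.8% |
| 0.5 | 15% to 48% | 4.1% / 4.6% | 81.1% / 82.4% |
| 0.8 | 9% to 59% | 3.8% / 4.8% | 81.3% / 83.7% |
| 1.0 | 7% to 65% | 4.2% / 5.8% | 81.6% / 85.1% |

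Dividing a percentage-point SD by 0.1875 gives its approximate log-odds SD, so 5, 10 and 15 points correspond to 0.27, 0.53 and 0.80. The two tables agree. The largest gain, 85.1 − 81.6 = 3.5 points, needs very wide center differences. In that row the CMH type I error also came out somewhat above 5%, so the figure should be read loosely.

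**4. Two recipients of one donor.** Repeating the simulation with an assumed donor log-odds SD of 1.0:

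- type I error, chi-square: 5.1% to 7.1%
- type I error, center-stratified CMH: 6.6% to 7.4%
- type I error, center-stratified test with donor-clustered variance: 4.8% to 5.4%

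Stratifying without clustering by donor does not control the error. At the widest center variation it raises it, from 5.1% to 6.6%, because it removes the conservatism that had partly masked the donor correlation.

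**The case against.** **The primary test is valid and the loss is small.** This stands as far as the strata are concerned. A reader might infer that the precision bought by stratification is lost. It is not: balance reduces the true variability of the simple risk difference whatever test follows, and only the reported standard error fails to show it. In a separate simulation with 288 donors and center SD 10 points, the true standard error was 0.0351 and the nominal one 0.0361. The power of the unadjusted test itself rises from 80.3% to 81.6% as centers diverge.

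**Intervals need not be too wide.** That reading requires the two recipients of one donor to be independent. With center SD 5 points and an assumed within-donor correlation of 0.1, the chi-square type I error was about 6.1%, so the intervals would be too narrow. This also stands. Donor clustering is a separate issue and adds no weight to the stratification point. It does determine how the fix must be built.

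**The stratifying center may explain little.** Donors are randomized, and the article does not say that kidneys are transplanted where the donor is managed. If they go elsewhere, the gain falls. Nothing has been quantified for number of kidneys.

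**The secondary model may be sound for its stated aim.** A reader might infer that it excludes treatment. The printed list, in a condensed article, neither includes nor excludes the arm. A reader might also infer that "procurement variables: cold and warm ischemia durations" makes the model wrong. For a search for predictors of DGF these are legitimate terms. They become a problem only if the model is used to estimate the treatment effect. Even then bias is a risk and not a certainty, since care is blinded and management is stated to be similar in both groups.

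**Conclusion.** The mismatch is real: the strata used to randomize do not enter the primary comparison, and the secondary model as printed does not supply an adjusted treatment effect. The consequence is modest. On this account the primary test is valid and slightly conservative, with type I error of about 4% to 4.5% when centers differ. A center-stratified test would gain about 0 to 3.5 power points at 588 recipients. These sizes assume between-center log-odds SDs from 0 to 1.0, near-equal centers, two recipients per donor, and outcomes independent within donor. None of the stated sample-size figures is wrong, and this point gives no reason to raise them.

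The documents do not support a claim of inflated type I error from ignoring the strata, of treatment being left out of the model on purpose, or of bias from the ischemia terms in the model's stated use.

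**What to change.** 1. In Data analysis, make the primary treatment comparison account for center and number of kidneys as randomized. Fit center as a random effect, or pool small centers if strata are sparse: 588 / 32 is only about 18 recipients per stratum on average.
2. Report a marginal risk difference with its confidence interval, in keeping with the 10-point difference used to plan the trial.
3. Use donor-clustered standard errors in the same analysis. Stratification should not be added without them.
4. State the purpose of the secondary logistic model. If an adjusted treatment effect is to be reported from it, list treatment, the strata and only covariates that dosing cannot affect: donor variables recorded before dosing, recipient weight and dialysis duration. Keep cold and warm ischemia durations in a separate exploratory risk-factor model.

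The cost is wording and slightly more analysis work, with possible pooling of small centers. The strata are known at randomization and ischemia times are already collected, so this change needs no extra patients or data. It should be fixed before unblinding.

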### Trial intervention

After randomization, donors with a beating heart will receive a single dose of 2.5 mg kg^−1^ of cyclosporine A (diluted to obtain a 5 mg mL^−1^ concentration corresponding to an infusion of 0.5 mL kg^−1^; Sandimmun**®**, Novartis Pharma, Rueil-Malmaison, France) or an equivalent volume of placebo (glucose 5% solution 0.5 mL kg^−1^) in the 2 h before the harvesting of kidneys in the operating theater. The management of the donors, the organs and the transplanted patients will be performed according to national guidelines [16] similarly in both groups.

### Outcomes

➢ Primary outcome: rate of DGF defined by the need for at least one dialysis session within the first 7 days after kidney transplantation➢ Secondary outcomes:○ Rate of SGF defined by a urine output of less than 1000 mL on day 1 after transplantation, or a decreased of less than 30 and 70% in creatinine plasma concentration, respectively, on days 3 and 7 after transplantation○ Combined rate of DFG + SGF○ Mild DGF defined by a serum creatinine reduction ratio from post-transplant day 1 to day 2 less than or equal to 30% plus 24-h urine creatinine excretion on day 2 greater than 1000 mg○ Severe DGF defined by a serum reatinine reduction ratio from post-transplant day 1 to day 2 less than or equal to 30% plus 24-h urine creatinine excretion on day 2 less than or equal to 1000 mg○ Duration of in-hospital length of stay (post-transplantation hospitalization)○ Daily urine output on days 1, 3 and 7○ Creatininemia and estimated creatinine clearance by the Modification of Diet in Renal Disease (MDRD) formula [17] on days 1, 3 and 7○ Rate of primary graft dysfunctions on day 1 defined by the absence of immediate renal function (anuria)○ Time between transplantation and normalization of graft function in patients presenting a DGF○ Function of kidney transplants at 1 year: kidney graft dysfunction defined by a clearance creatinine less than 30 mL min^−1^ estimated by the MDRD formula or total dysfunction defined by a persistent hemodialysis○ In-hospital and 1-year mortality rate of transplanted patients

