#### Sample size

The sample size was determined to obtain 80% power to detect a 10% difference for rate of DGF (as defined in the primary endpoint section) at day 7 between the two groups, as this difference is considered to be clinically significant. In accordance with previous studies [7, 8], we hypothesized that 30% of the patients in the placebo group and 20% of the patients in the intervention group will develop DGF. With the threshold for statistical significance set at a *p* value of 0.05 (two-sided alpha), these calculations showed that 588 participants (recipients) are needed (294 per group). Assuming that a potential 10% of participants will be lost to follow-up (for the primary or the secondary endpoints), a total of 648 recipients needs to be included. Secondary outcomes will be compared between the two groups: using the chi^2^ test or Fisher’s exact test for categorical variables and Student’s *t* test for continuous variables.

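### Slow graft function is not separated from dialysed DGF, and first-week creatinine and MDRD comparisons have no rule for dialysed recipients

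*Protocol article*

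**What the plan says.** All of this is in the protocol article.

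- **Primary outcome (Outcomes):** "rate of DGF defined by the need for at least one dialysis session within the first 7 days after kidney transplantation".
- **SGF (Outcomes):** "Rate of SGF defined by a urine output of less than 1000 mL on day 1 after transplantation", or alternatively "a decreased of less than 30 and 70% in creatinine plasma concentration, respectively, on days 3 and 7 after transplantation". Neither criterion mentions dialysis.
- **Combined outcome (Outcomes):** "Combined rate of DFG + SGF". The text does not say how the two are combined.
- **Early renal function (Outcomes):** "Creatininemia and estimated creatinine clearance by the Modification of Diet in Renal Disease (MDRD) formula [17] on days 1, 3 and 7". No rule is given for recipients on dialysis.
- **The one outcome restricted by DGF status (Outcomes):** "Time between transplantation and normalization of graft function in patients presenting a DGF".
- **Analysis (Sample size):** "Secondary outcomes will be compared between the two groups", by chi-squared or Fisher's exact test for categorical outcomes and "Student’s *t* test for continuous variables". No subset is named.

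The Background section names SGF and first-week serum creatinine among the main secondary objectives. It quotes frequencies of 30% for DGF and 40–60% for SGF without saying whether they overlap. The Data registration section shows that first-week dialysis is recorded, as are creatinine, MDRD clearance and 24-hour urine output on days 1, 3 and 7.

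**The concern.** There are two separate problems, and they do not act in the same way.

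**Overlap.** A dialysed recipient with low urine output on day 1 meets both definitions. The SGF comparison then carries over part of the DGF effect and is not independent evidence of better early function. Dialysis also clears creatinine, so some dialysed recipients may show the required fall without graft recovery and leave the creatinine criterion. The first mechanism moves the DGF effect into SGF and the second takes some of it out. A reader of the SGF rate cannot tell which dominates.

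**Altered values.** Serum creatinine on days 3 and 7, and the clearance computed from it, reflect dialysis as well as the graft. If treatment works as the plan supposes, more placebo recipients are dialysed, so more of the worst placebo values are artificially improved. A two-group comparison of means would then understate a real benefit.

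**Working it through.** **The plan's own figure.** With 30% v 20%, two-sided alpha 0.05 and 80% power, the pooled formula gives

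n per group = [1.96 × √(2 × 0.25 × 0.75) + 0.8416 × √(0.3 × 0.7 + 0.2 × 0.8)]² / 0.10² = 293.2, rounded up to 294, or 588 in total.

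This reproduces the Sample size section. Nothing below changes it.

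**Overlap of SGF with DGF.** The DGF rates of 30% (placebo) and 20% (intervention) come from the Sample size section. Two shares are assumed: q, the share of dialysed recipients meeting the SGF criteria, and s, the share of non-dialysed recipients meeting them, each taken as equal in the two arms.

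- SGF on placebo = 0.3q + 0.7s
- SGF on intervention = 0.2q + 0.8s
- Difference (placebo minus intervention) = 0.10 × (q − s)

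With s = 0.3:

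| q | Placebo | Intervention | Difference (points) |
|---|---|---|---|
| 1.0 | 51% | 44% | +7 |
| 0.9 | 48% | 42% | +6 |
| 0.5 | 36% | 34% | +2 |
| 0.2 | 27% | 28% | −1 |

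Treatment has no effect on SGF among non-dialysed recipients in any row. The whole difference comes from DGF through the overlap, and its sign depends on whether q exceeds s.

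**Two simple exclusions do not solve this.** With s = 0.3, recoding dialysed recipients as not SGF but keeping them in the denominator gives 0.7 × 0.3 = 21% v 0.8 × 0.3 = 24%, which appears to go against treatment. Removing them from the denominator gives 30% v 30%, but compares subsets selected by a post-randomization event.

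**Combined rate.** As a union it is 0.30 + 0.21 = 51% v 0.20 + 0.24 = 44%, whatever the value of q.

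**Three exclusive classes.** Immediate function / SGF without dialysis / DGF are 49 / 21 / 30% on placebo and 56 / 24 / 20% on intervention. Every recipient is counted once and the shift is visible: 30% v 20% for DGF, and 51% v 44% for SGF or worse.

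**Creatinine.** Assumed day-7 means are 160 µmol/L without DGF and 600 µmol/L with DGF before any clearance by dialysis. Dialysis lowers the latter by a fraction f.

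Difference = 0.10 × [600 × (1 − f) − 160]

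- f = 0: 292 v 248, difference 44 µmol/L
- f = 0.1: 0.10 × (540 − 160) = 38 µmol/L
- f = 0.3: 238 v 212, difference 26 µmol/L
- f = 0.5: 202 v 188, difference 14 µmol/L

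A second assumed set, with 180 µmol/L without DGF, gives 42 µmol/L when the DGF mean is 600. This falls to 22, 12 and 2 µmol/L when dialysis brings that mean to 400, 300 and 200. The direction is the same in both sets.

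**The case against.** Several stronger readings are tempting, and the document does not support them.

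- A reader might infer that all these outcomes are biased toward no difference. For SGF this is not so: overlap alone creates a difference away from zero (+6 points at q = 0.9, s = 0.3). The criteria are alternatives, and clearing creatinine does not affect day-1 urine output. Nor do creatinine and MDRD clearance double-count DGF; dialysis distorts them.
- A reader might take the combined rate as a sum of overlapping rates. The planned chi-squared or Fisher test needs one yes/no status per recipient, so a union is the natural reading, and overlap does it no harm. Only the wording needs settling.
- A reader might say the plan includes dialysed values. The article is silent on this, and a full protocol or analysis plan, not shown, may set a rule. That is a fair limit on the creatinine point. It does not cure the SGF definition, which the article does state.

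Two further objections carry weight. The creatinine means and reductions are not from the document, and DGF needs only one session at any time in the week, so a day-7 sample may be little affected; the f = 0.1 line shows how small the loss could then be. And whether MDRD clearance should be compared at all in the first week is a matter of preference, not an error in the plan.

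**Conclusion.** The point holds for secondary outcomes only. As defined, SGF overlaps the primary endpoint by an amount that cannot be known in advance, and the direction of the net effect on its arm difference is not predictable (+7 to −1 points over the range shown, given 30% v 20% DGF and s = 0.3 in both arms). Applied as written, the t test of creatinine and MDRD clearance on days 3 and 7 would understate a true benefit, because dialysis-lowered values would be more frequent on placebo. In the main illustration the difference of 44 µmol/L becomes 26 or 14 at reductions of 30% or 50%. The direction rests on the plan's own DGF scenario; the size rests on assumed means and reductions. The primary endpoint and the 588 recipients stand. A change is worthwhile because SGF and first-week creatinine are among the main secondary objectives.

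**What to change.** 1. Classify every recipient once: immediate function, SGF (criteria met and no dialysis by day 7), or DGF (dialysis by day 7). Compare the three ordered classes in all recipients, for example with an ordinal model or a rank test. Do not interpret on its own an SGF rate from which dialysed recipients have been removed or recoded.
2. State that the combined rate is the union of DGF and SGF, counted once per recipient.
3. Compare day 3 and day 7 creatinine (and MDRD clearance, if kept) with a rank-based test that gives the worst rank to recipients already dialysed by that day. Report the raw values descriptively.

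**Cost.** This is a change of outcome and analysis wording. The classes and the day-7 ranking use data the article already lists. The day-3 ranking also needs the date of the first dialysis session; the article does not list this separately, so it should be confirmed in the case report form. The main drawback is that a rank-based result is not expressed in µmol/L.
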